## Abstract

**Background::**

In observational studies, drinking more water associates with a slower rate of kidney function decline; whether the same is true in a randomized controlled trial is unknown.

**Objective::**

To examine the 1-year effect of a higher vs usual water intake on estimated glomerular filtration rate (eGFR) in patients with chronic kidney disease.

**Design::**

Parallel-group randomized controlled trial.

**Setting::**

Nine centers in Ontario, Canada. Enrollment and randomization occurred between May 2013 and May 2016; follow-up for the primary outcome will continue until June 2017.

**Participants::**

Adults (n = 631) with stage 3 chronic kidney disease (eGFR 30-60 mL/min/1.73 m^2^) and microalbuminuria.

**Intervention::**

The high water intake group was coached to increase their oral water intake by 1.0 to 1.5 L/day (depending on sex and weight), over and above usual consumed beverages, for a period of 1 year. The control group was coached to maintain their usual water intake during this time.

**Measures::**

Participants provided 24-hour urine samples at baseline and at 6 and 12 months after randomization; urine samples were analyzed for volume, creatinine, osmolality, and the albumin-to-creatinine ratio. Blood samples were obtained at baseline and at 3- to 6-month intervals after randomization, and analyzed for creatinine, copeptin, osmolality, and electrolytes. Other measures collected included health-related quality of life, blood pressure, body mass index, and diet.

**Primary outcome::**

The between-group change in eGFR from baseline (prerandomization) to 12 months after randomization.

**Secondary outcomes::**

Change in plasma copeptin concentration, 24-hour urine albumin-to-creatinine ratio, measured creatinine clearance, estimated 5-year risk of kidney failure (using the 4-variable Kidney Failure Risk Equation), and health-related quality of life.

**Planned analysis::**

The primary analysis will follow an intention-to-treat approach. The between-group change in eGFR will be compared using linear regression. Supplementary analyses will examine alternative definitions of eGFR change, including annual percentage change, rate of decline, and rapid decline (a *P* value <0.05 will be interpreted as statistically significant if there is concordance with the primary outcome).

**Trial Registration::**

This randomized controlled trial has been registered at www.clinicaltrials.gov; government identifier: NCT01766687.

## What was known before

In observational studies, drinking more water associates with a slower rate of kidney function decline in adults.Whether supplemental water intake can preserve kidney function in patients with chronic kidney disease is unknown.

## What this adds

A common question in a kidney clinic is “How much water should I drink?” The Chronic Kidney Disease Water Intake Trial will provide new information on the 1-year effect of a higher vs usual water intake on kidney function, plasma copeptin, microalbuminuria, and quality of life in adults with chronic kidney disease.

## Introduction

The purported benefits of drinking more water are largely untested, with many unfounded claims in the popular media.^1-3^ However, there is now a growing body of evidence on the specific effect of increased water intake on the kidney.^4^ Increased water intake has been shown to reduce the risk of kidney stones (a greater urine flow rate may lower the supersaturation of calcium oxalate, calcium phosphate, and uric acid) and lower the risk of stone formation,^5-7^ and guidelines recommend drinking water to achieve a urine output of 2.0 to 2.5 L/day to reduce the risk of stone recurrence.^8,9^ In polycystic kidney disease, there is some evidence that increased water intake may slow the growth of renal cysts via suppression of vasopressin;^10-12^ however, this has yet to be confirmed in a clinical trial.^13-15^ Most recently, chronic dehydration and volume depletion resulting from extreme occupational heat stress has been identified as a likely cause of an epidemic of chronic kidney disease in Central America.^16-20^ Scientists are now investigating the epidemiology of heat-stress nephropathy across the globe.^20-23^

The relationship between water intake and the estimated glomerular filtration rate (eGFR) has been investigated in several observational studies; however, results are mixed.^4^ In a retrospective analysis of adults patients with chronic kidney disease in the Modification of Diet in Renal Disease study, higher urine volumes were associated with a greater decline in eGFR; however, this association lost significance after controlling for diuretics and antihypertensive medication use.^24^ By contrast, in a prospective cohort study of adults free of chronic kidney disease at study entry, higher urine volumes at baseline were associated with a slower decline in eGFR over 7 years, and those with the largest urine volumes (>3L/day) were the least likely to demonstrate a rapid decline in eGFR (defined as a decline ≥5%/year).^25^ These results persisted after adjusting for age, gender, baseline eGFR, medication use for hypertension (including diuretics), proteinuria, diabetes, and cardiovascular disease. Interestingly, in studies examining the effects of plain water intake vs other fluids, increased intake of plain water is more often associated with a decreased risk of chronic kidney disease; however, increased intake of sweetened beverages is associated with an increased risk.^26-32^ Similarly, while the risk of kidney stone recurrence is reduced with greater intake of plain water,^8,9^ the risk of stone recurrence is increased with greater intake of sweetened beverages, possibly due to the high fructose content, which has been shown to increase the urinary excretion of calcium, oxalate, and uric acid.^33-36^

While these studies provide preliminary evidence that drinking more water may have a beneficial effect on kidney function, it remains unknown whether supplemental water intake can benefit patients with chronic kidney disease. Urine concentrating capacity is reduced as kidney function declines, and thus some patients with chronic kidney disease may have high 24-hour urine volumes while being slightly volume depleted, which makes it difficult to isolate causal effects in observational studies. To provide further insight into this question, we designed a randomized controlled trial to examine the effects of an increased vs usual water intake on kidney function in adults with chronic kidney disease—the Chronic Kidney Disease Water Intake Trial (WIT). In this parallel-group trial, participants randomized to the hydration group are coached to drink 1.0 to 1.5 L of water per day (depending on weight and sex), over and above their usual fluid intake, for 1 year. Participants randomized to the control group are asked to continue with their usual fluid intake during this time. The primary outcome of this trial is change in kidney function at 1 year. The trial design and methods were informed by a 6-week randomized pilot trial, which confirmed the safety and feasibility of asking adults with chronic kidney disease to increase their water intake by 1.0 to 1.5 L/day.^37,38^ The current protocol describes the objectives, methods, and analytic plan for the WIT main trial. To our knowledge, this will be the first clinical trial on record to test the impact of a sustained increase in water intake over 1 year in patients with chronic kidney disease.

**Primary objective**: To examine the effect of increased water intake over 1 year on change in eGFR among patients with chronic kidney disease.**Secondary objectives**: To examine the effect of increased water intake over 1 year on change in plasma copeptin concentration, 24-hour urine albumin-to-creatinine ratio, measured creatinine clearance, the estimated 5-year risk of kidney failure (using the 4-variable Kidney Failure Risk Equation^39^), and health-related quality of life. We will also establish the safety of increased water intake in this population by monitoring for electrolyte disturbances, particularly hyponatremia.

## Methods

### Design, Setting, and Participants

WIT is a parallel-group, open-label, 9-center randomized controlled trial. Recruitment and randomization (detailed below) occurred between May 2013 and May 2016; follow-up for the primary outcome will continue until June 2017 (trial registration: www.clinicaltrials.gov; government identifier: NCT01766687). Ethics approval was obtained from Western University’s Health Sciences Research Ethics Board.

Adult patients with stage 3 chronic kidney disease were recruited from 9 chronic kidney disease clinics across Southwestern Ontario (Canada) in London (3 centers), Guelph (1 center), Hamilton (1 center), Oakville (2 centers), and Windsor (2 centers). The patient’s nephrologist invited interested potential participants to speak with a research assistant who explained the study and confirmed study eligibility (patient eligibility criteria are fully detailed in Table 1). All participants had to have stage 3 chronic kidney disease (eGFR 30-60 mL/min/1.73 m^2^) and microalbuminuria (defined as albumin/creatinine >2.8 mg/mmol if female, or >2.0 mg/mmol if male, or trace protein or greater from a random spot urine sample on an Albustix).^40^ Exclusion criteria (fully detailed in Table 1) included self-reported fluid intake ≥10 cups/day or a 24-hour urine volume ≥3L; a history of kidney stones in the past 5 years; or currently taking lithium, hydrochlorothiazide >25 mg/day, indapamide >2.5 mg/day, furosemide >40 mg/day, or metolazone >2.5 mg/day.

**Table 1. table1-2054358117725106:** Eligibility Criteria for the Chronic Kidney Disease Water Intake Trial.

Inclusion criteria
● Age between 18 and 80 years. ● Able to provide informed consent and willing to complete follow-up visits. ● Estimated glomerular filtration rate between 30 and 60 mL/min/1.73 m^2^. ● Trace protein or greater (Albustix) or urine albumin/creatinine ratio ≥2.8 mg/mmol (if female) or ≥2.0 mg/mmol (if male) from a random spot urine sample. ● Ability to read and speak English.
Exclusion criteria
● Self-reported fluid intake ≥10 cups/day or 24-hour urine volume ≥3 L. ● Enrolled in another randomized controlled trial that could influence the intervention, outcomes, or data collection of this trial (or previously enrolled in this trial). ● Received one or more dialysis treatments in the past month. ● Received a kidney transplant in past 6 months. ● Pregnant or breastfeeding. ● History of kidney stones in the past 5 years. ● Less than 2 years’ life expectancy. ● Serum sodium <130 mEq/L without suitable explanation. ● Serum calcium >2.6 mmol/L without suitable explanation. ● Currently taking hydrochlorothiazide >25 mg/day, indapamide >2.5 mg/day, furosemide >40 mg/day, or metolazone >2.5 mg/day. ● Currently taking lithium. ● Currently under fluid restriction (<1.5 L a day) for kidney disease, heart failure, or liver disease, AND meets any of the following criteria (1) end-stage disease (heart left ventricular ejection fraction <40%, NYHA class 3 or 4, or end-stage cirrhosis) or (2) any hospitalization for heart failure, ascites, and/or anasarca. ● Significant gastrointestinal disease (eg, inflammatory bowel disease or Crohn disease)

*Note.* NYHA = New York Heart Association.

After providing written informed consent, participants were asked to provide a prerandomization baseline 24-hour urine sample within 2 weeks (details provided in Data Collection and Measures section) to confirm that urine volume was below 3 L/day; participants were not randomized until their 24-hour urine samples were collected and analyzed.

### Randomized Allocation

Once study eligibility was confirmed, a research assistant contacted the participant by telephone to complete the randomization; concealed randomized allocation occurred by computer-generated randomization while the participant was on the phone. Participants were randomized (1:1) in random permuted blocks of varying sizes to the hydration group or the control group, stratified by center and gender. By necessity, research staff and participants were aware of the randomized group assignment; however, outcome assessors (technicians performing the laboratory measurements for the primary and secondary outcomes) are blinded to the random allocation, and the trial statistician will be blinded to patient allocation for the primary analysis.

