Participants provided nonfasting 10-mL blood samples at baseline, at 3 weeks after randomization, and then again at 3-month intervals after randomization until 12-months. Blood samples could be provided at the study research center or a local laboratory facility as described above. Serum creatinine was measured using the isotope dilution/mass spectroscopy–traceable enzymatic method, and eGFR was calculated using the Chronic Kidney Disease Epidemiology Collaboration (CKD-EPI) equation.^47^ Serum sodium was measured using indirect ion-selective electrodes. Other measures analyzed from blood samples at baseline and at 6 and 12 months after randomization included urea concentration (measured with enzymatic photometric methods), osmolality (measured by freezing point depression using an advanced instrument Micro-Osmometer), hematocrit (measured using Beckman Coulter automated cell counters), cystatin C (measured using immunonephelometry), glycated hemoglobin (HbA1c) (measured using nonporous ion exchange high-performance liquid chromatography), and copeptin (a glycosylated peptide that is coreleased with vasopressin from the hypothalamus^48,49^); copeptin was measured from nonfasting 150 µL blood samples, stored at −80°C, and analyzed in batches using the sandwich immunoluminometric assay (B.R.A.H.M.S. AG, Hennigsdorf/Berlin, Germany) as described by Morgenthaler et al.^48,50^ To examine whether there was any lasting effect of the intervention after coaching stopped at 12 months, we collected data on serum creatinine from participant medical charts 18 to 24 months after randomization.

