### Analysis

We will use SAS version 9.3 (SAS Institute Inc, Cary, NC) for all statistical analysis.

The primary analysis will follow an intention-to-treat approach. The between-group difference on change in eGFR (calculated as eGFR at 12 months minus eGFR at baseline) will be analyzed using linear regression. The following prespecified covariates (measured at baseline) will be adjusted for in the primary analysis: age (in years), sex, obesity (body mass index ≥30 kg/m^2^), smoking status (current smoker: yes/no), presence of diabetes, albuminuria (mg/d), and use of any of the following medications: an angiotensin-converting enzyme inhibitor or angiotensin receptor blocker, diuretics, beta blockers or calcium channel blockers, and statins. We will include a missing data indicator value for each covariate.^56^ We expect that 12-month data on eGFR will be missing for <5% of participants due to death and <10% due to missing data or study withdrawal. For patients who were randomized but are missing a 12-month eGFR value, we will use recommended model-based multiple imputation methods to impute the final eGFR value.^57-59^ We will perform sensitivity analyses, including a complete-case analysis, to investigate whether conclusions are sensitive to assumptions about the missing-data mechanism.^57-59^

We will report the primary outcome as the absolute difference in 12-month eGFR change between randomized groups with a 95% confidence interval. Our current sample size of 631 randomized participants will provide 80% power to detect a difference of at least 1.8 mL/min/1.73 m^2^ between intervention groups (α = 0.05, independent samples *t* test, assuming a standard deviation of 8), which represents a small-to-moderate effect size. The primary analysis will be performed 12 months after the last patient has been randomized (date of final follow up expected in June 2017).

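### Center is a randomization stratum but is missing from the stated covariates of the primary model, so the reported standard error may be somewhat too large

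*Protocol article*

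**What the plan says.** On design, the article states that "WIT is a parallel-group, open-label, 9-center randomized controlled trial". Under Randomized Allocation it says: "Participants were randomized (1:1) in random permuted blocks of varying sizes to the hydration group or the control group, stratified by center and gender". Nine centers and two sexes make 18 strata.

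On analysis, the Analysis section names the adjustment set outright: "The following prespecified covariates (measured at baseline) will be adjusted for in the primary analysis: age (in years), sex, obesity", and the list goes on to "smoking status (current smoker: yes/no), presence of diabetes, albuminuria (mg/d), and use of any of the following medications", followed by four medication groups (ACE inhibitor or angiotensin receptor blocker; diuretics; beta blocker or calcium channel blocker; statins). Taking gender at randomization and sex in the model as the same variable, one of the two stratification factors is in the list and the other is not. No other section brings center into the primary model as a fixed effect, random effect or stratum.

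The Secondary Outcomes section refers the continuous outcomes (copeptin, creatinine clearance, albuminuria, kidney failure risk) back to the same regression, so they inherit the omission.

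**The concern.** Permuted blocks within center keep the two arms close to equal in number in each center. Differences between centers in mean eGFR change therefore largely cancel from the treatment comparison, and the true sampling variance of the estimate is smaller than under simple randomization. A regression without center does not know this. It leaves the between-center variation in the residual and reports a standard error that contains it.

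What is at stake is efficiency and the match between design and analysis: a confidence interval wider than it need be, and a test that rejects less often than its nominal level. Because the article spells out the covariate list, this is a choice it has fixed rather than a detail left to a fuller document. It gives no reason for keeping one stratification factor and leaving out the other.

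**Working it through.** **Inputs from the article (Analysis section).** 631 randomized, 1:1, so 315.5 per arm; difference 1.8 mL/min/1.73 m²; standard deviation 8; α = 0.05; independent-samples t test. Sidedness is not stated; two-sided reproduces the figure.

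**Assumed input.** ρ, the share of residual variance in eGFR change that lies between centers after the listed covariates. The article does not give it; 0 to 0.10 is shown.

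**Step 1: the stated power.** SE = 8 × √(2/315.5) = 0.637. Power = Φ(1.8/0.637 − 1.96) = Φ(0.866) = 80.7% (80.6% by the noncentral t). The sample size formula gives 311 per arm, 622 in all. The stated 80% with 631 is reproduced.

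**Step 2: what leaving out center does.** With arms balanced within center:

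- true SE = 0.637 × √(1 − ρ)
- SE reported without center ≈ 0.637
- reported/true = 1/√(1 − ρ)
- true type I error without center = 2Φ(−1.96/√(1 − ρ))
- power without center = Φ((1.8/0.637 − 1.96)/√(1 − ρ))
- power with center = Φ(1.8/(0.637 × √(1 − ρ)) − 1.96)

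For ρ = 0.10, √(1 − ρ) = 0.949. The ratio is 1/0.949 = 1.054, the type I error 2Φ(−2.066) = 3.9%, power without center Φ(0.866/0.949) = 81.9%, and power with center Φ(1.8/0.604 − 1.96) = 84.6%.

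| ρ (assumed) | Reported/true SE | Type I error without center | Power without center | Power with center | Gain (points) |
|---|---|---|---|---|---|
| 0 | 1.000 | 5.0% | 80.7% | 80.7% | 0 |
| 0.01 | 1.005 | 4.9% | 80.8% | 81.1% | 0.3 |
| 0.02 | 1.010 | 4.8% | 80.9% | 81.5% | 0.5 |
| 0.05 | 1.026 | 4.4% | 81.3% | 82.6% | 1.3 |
| 0.10 | 1.054 | 3.9% | 81.9% | 84.6% | 2.7 |

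Gains are taken from unrounded powers.

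**Step 3: check by simulation.** Nine centers of unequal size, two sexes, blocks of 2, 4 or 6 within the 18 strata, 631 patients, no treatment effect, 4,000 runs per setting. Block and center sizes are assumptions, and sex was the only other covariate.

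| ρ | Model | Mean reported SE | SD of estimates | Type I error |
|---|---|---|---|---|
| 0.05 | without center | 0.634 | 0.622 | 4.6% |
| 0.05 | with center | 0.620 | 0.622 | 5.2% |
| 0.10 | without center | 0.632 | 0.588 | 3.5% |
| 0.10 | with center | 0.605 | 0.587 | 4.5% |

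The Monte Carlo error of a rejection rate near 5% is √(0.05 × 0.95/4000) = 0.34 points, so 4.6% and 3.5% agree with the formula's 4.4% and 3.9%. The SD of the estimates is practically the same with and without center; what differs is the reported standard error. In the ρ = 0.10 setting that SD came out somewhat below the expected 0.604. In the companion run with a true difference of 1.8 it was 0.598 with center, closer to the reported 0.605.

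**The case against.** The strongest reply is that nothing shows center to matter for this outcome. The endpoint is a within-patient change, so a stable offset between clinics or laboratories cancels when the same laboratory is used at both visits. The creatinine assay is described as traceable to a reference method. Laboratory need not follow center either: "Blood samples could be provided at the study research center or a local laboratory facility as described above". All nine clinics lie in one region, and the covariates already in the model would absorb part of any difference in case mix or prescribing. This stands. It means the laboratory route is weak support, that ρ could be close to zero, and that the 10% row is an assumed extreme rather than an expectation. It does not remove the mismatch between the allocation and an explicit covariate list.

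A reader might infer more than the article supports:

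- **That the standard error is too large as a matter of fact.** It is so only if center is prognostic after adjustment, and no figure is given.
- **That the model adjusts for nothing but sex.** That is true only of the two stratification factors; the model has about ten covariates.
- **That the result would be biased or the test invalid.** The estimate is unbiased, and the error goes in the conservative direction.
- **That the gain from stratifying is thrown away.** The allocation still reduces the true variance; only the reported standard error fails to show it.
- **That the sample size is undermined.** The 80% comes from an unadjusted t test and does not depend on center.
- **That center is left out of the imputation.** The article does not list the imputation variables, so this is not shown.

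**Conclusion.** The mismatch is certain: center is a stratification factor and is absent from the stated adjustment set of the primary model, and hence of the continuous secondary outcomes. The consequence is conditional and small. If center explains between 0 and 10% of the residual variance in eGFR change, the reported standard error is inflated by 0 to about 5% and a nominal 5% test operates at 5.0% down to 3.9%. These sizes rest on the assumed share, on near balance of the arms within centers, and on the planning standard deviation of 8. A positive primary result would not be called into question. A result just short of significance could owe a little to the conservative standard error. This is a worthwhile improvement in efficiency and coherence, not a threat to validity.

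**What to change.** Add center to the covariates of the primary regression and of the continuous secondary-outcome regressions, as fixed effects, or as a random intercept if some centers prove small (center sizes are not reported). Sex is already there. Include center in the multiple imputation model as well, so that it matches the analysis model. If center is left out on purpose, state the reason.

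The cost is 9 − 1 = 8 degrees of freedom, set against 631 patients, or about 536 with an observed outcome if the expected losses reach their upper limits of 5% and 10% (631 × 0.85). Center is known for everyone randomized, so no data collection is needed. The trial statistician is to be blinded for the primary analysis, so the change can be recorded before any comparison by arm. It is one line of model wording.
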